### Procedures

This study was reviewed and approved by Advarra, the H. Lee Moffitt Cancer Center institutional review board (IRB) and is registered on ClinicalTrials.gov (NCT05645146). After completion of a brief online pre-screener, potential participants are contacted by research staff via phone to complete a more detailed screening. All eligible individuals are invited to participate. A detailed description of the study is provided, and verbal informed consent is obtained. Individuals who decline or are ineligible are referred to other cessation programs. Individuals who meet all eligibility criteria and consent to participating in the study complete the baseline assessment either over the phone with a research coordinator or via a secure electronic REDCap link sent via text message or email based on their preference. Following completion of the baseline assessment, participants are randomized to MAPS + or ST using a 1:1 ratio with a block size of 4 following stratification on the following variables: daily vs. nondaily smoking; CIN and early cancer stages (Stages I and Stage II) vs. advanced cancer stages (Stage III and Stage IV), and pending or in active treatment vs. completed treatment. The randomization sequences were created by the study statistician and implemented in REDCap.

Assessments occur at baseline, 3, 6, 12, 18 and 24 months and take approximately 20 min to complete (see Table 1). Participants are given the option to complete the assessments via phone or via a hyperlink as a REDCap-administered self-assessment. Compensation is provided after each assessment is completed (6 assessments x $30 = $180). Participants who report abstinence at any follow-up point are mailed a cotinine test. Compensation for returning cotinine tests is $30 per assessment.

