### Intervention conditions

#### Standard treatment

Participants randomized to ST are electronically connected with Tobacco Free Florida by the study team. Treatment consists of the standard treatment offered by Tobacco Free Florida, which is consistent with the Treating Tobacco Use and Dependence Clinical Practice Guideline [31, 32] in that treatment content is drawn from cognitive-behavioral and motivational interviewing techniques.

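### A single, published block size of 4 within strata would let anyone who tracks past assignments in a known stratum know up to about a third of upcoming assignments for certain

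*Protocol article*

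**What the plan says.** All from the protocol article.

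- **Allocation (Procedures).** "participants are randomized to MAPS + or ST using a 1:1 ratio with a block size of 4 following stratification". No variation in block size is mentioned.
- **Strata (Procedures).** Three two-level factors. The first is smoking frequency (daily or not). The second is disease extent, which pools CIN with Stage I-II cancer and sets them against Stage III-IV. The third is treatment status: "pending or in active treatment vs. completed treatment". That makes 2 × 2 × 2 = 8 strata. Site is not a factor, so there are eight sequences in all.
- **Generation and concealment (Procedures).** "The randomization sequences were created by the study statistician and implemented in REDCap".
- **Order of events (Procedures).** First, "potential participants are contacted by research staff via phone to complete a more detailed screening". Verbal consent and the baseline assessment come next, and only then the allocation: "Following completion of the baseline assessment, participants are randomized to MAPS + or ST". On invitation: "All eligible individuals are invited to participate".
- **Visibility of the arms.** Under Standard treatment: "Participants randomized to ST are electronically connected with Tobacco Free Florida by the study team". The MAPS+ section describes six counselor calls plus text messages. No masking of staff is described anywhere.
- **Status.** The abstract says that recruitment started in December 2022 and is still going on.

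**The concern.** Concealing an allocation list protects enrolment only if the next assignment cannot be worked out from earlier ones. With a constant block of 4 at 1:1, the fourth assignment in a block always follows from the first three, and the third follows whenever the first two match. REDCap hides the list but not this pattern, and the people who arrange or deliver treatment learn each assignment as it is made.

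If the same knowledge reached the staff who screen, describe the study and take consent, it could affect how hard a caller is encouraged or how quickly they are followed up. The primary outcome is self-reported abstinence. The Discussion reports that 67% of participants in the team's previous trial were not ready to quit at enrolment, so candidates probably differ widely on something that plausibly predicts quitting. Uneven encouragement between arms could then appear as a treatment effect.

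**Working it through.** The plan gives no figure for predictability, so there is nothing to reproduce first.

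**Inputs.** Block size 4 and ratio 1:1 (Procedures); 8 strata (Procedures); N = 340 (Recruitment and participants).

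**Step 1: certain assignments in one block.** A block with two places per arm has 6 equally likely orders. An assignment is certain once one arm's two places are used.

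| Position | Chance it is certain | Chance the best guess is right |
|---|---|---|
| 1 | 0 | 1/2 |
| 2 | 0 | 2/3 |
| 3 | 1/3 (first two match) | 1/3 × 1 + 2/3 × 1/2 = 2/3 |
| 4 | 1 | 1 |

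Certain: (0 + 0 + 1/3 + 1) / 4 = (4/3) / 4 = 33.3%.

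Best guess, choosing the arm with more places left: (1/2 + 2/3 + 2/3 + 1) / 4 = (17/6) / 4 = 70.8%.

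**Step 2: the whole trial.** If every block were filled and every stratum tracked, 0.333 × 340 = 113 assignments would be certain. Final blocks are usually incomplete. A simulation of 340 participants over 8 strata gave 32.3% with equal strata and 32.3% with a skewed mix. The skewed mix is an assumption, since the article gives no distribution: 85% in one smoking-frequency level, 95% CIN or early stage, 80% in one treatment-status level. In both cases 0.323 × 340 ≈ 110. Eight strata make tracking more laborious but hardly change the predictable share.

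**Step 3: other block designs.** By the same enumeration:

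| Fixed size | Certain | Best guess right |
|---|---|---|
| 4 | 33.3% | 70.8% |
| 6 | 25.0% | 68.3% |
| 8 | 20.0% | 66.6% |

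Now let sizes vary at random with equal probability, and assume that the observer knows the set of sizes and where each block starts. Only a block of the largest size can then give a certain assignment.

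- Sizes 4 and 6: (1/2 × 6 × 0.25) / 5 = 0.75 / 5 = 15%.
- Sizes 4, 6 and 8: (1/3 × 8 × 0.20) / 6 = 0.533 / 6 = 8.9%.

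Simulation gave 15.0% and 8.9%.

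Under the same assumption the best guess falls less. With sizes 4, 6 and 8 it is right (4 × 0.708 + 6 × 0.683 + 8 × 0.666) / 18 ≈ 68% of the time. Varying the size removes most of the certainty. It removes little of the guessing advantage for someone who can see block starts and running counts.

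**The case against.** The strongest reply is that the arithmetic describes an observer whom the article does not show to exist.

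- The research staff who screen and the study team that makes quitline referrals are not stated to be the same people. A condensed article commonly leaves access to allocations to the full protocol.
- Stage and treatment status belong to the history measure that Table 1 schedules at baseline. If screening does not collect them, the stratum, and so the relevant block, is unknown at consent.
- Participants choose between a phone baseline with a coordinator and a REDCap link. On the link route they set the completion time and enter the answers themselves.
- Everyone eligible is invited, and the trial deliberately takes people at any level of readiness.
- Motivation is measured at baseline, and the General analytic approach makes any baseline variable that differs at p < .10 a covariate in the primary analyses.

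All of this stands, and it limits the claim. A reader might infer that staff already know a third of assignments, that they control baseline timing and stratum coding, or that the analysis could neither detect nor correct the result. The article supports none of these. It does not say that screeners see allocations or schedule the baseline, and an imbalance in measured motivation would be examined and, past the threshold, adjusted for.

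The reply does not remove the weakness. The invitation rule governs who is asked, not how persuasively or how persistently. REDCap cannot hide what past assignments reveal. The covariate rule reaches only recorded variables that cross its threshold, so a staff member's unrecorded impression of a caller would pass through.

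**Conclusion.** The point holds as a potential, conditional weakness in a stated design choice. It is neither an internal contradiction nor evidence that selection has occurred. Within a known stratum whose history is tracked, 33.3% of assignments per filled block are certain (about 110 of 340 over the trial), and the best guess is right about 71% of the time.

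This rests on three assumptions: that the block size stays at 4 as stated, that someone involved before randomization can see earlier assignments by stratum, and that this person knows the candidate's stratum in time to act. The article settles only the first. That the trial is unmasked is itself inferred from the nature of the arms and the absence of any masking statement. The resulting bias cannot be sized from the document. The change is worth making because it is cheap and, with recruitment open at publication, still useful.

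**What to change.** 1. For the remaining participants, append to REDCap a new list for each stratum with block sizes varied at random (for example 4, 6 and 8), starting when that stratum's current block is complete. Do not disclose the sizes to screening and consenting staff, or in print, until enrolment closes. Moving to a larger fixed size is not enough, since 25% or 20% would remain certain.
2. Keep running allocation tallies from screening and consenting staff, and document who can see assignments. This matters as much as the new lists, because varied sizes alone do little against informed guessing. If that separation already exists, recording it would largely answer the concern.

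**Cost.** The change is a protocol modification, and the Data and safety monitoring plan sends all modifications for IRB approval. An incomplete final block can leave a stratum unbalanced by at most half the block size, so the limit rises from 2 to 4 participants where the last block has size 8. This matters mainly in small strata. Endpoints, sample size and treatment are untouched. The benefit depends on how many participants are still to be enrolled, which the article does not give.

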### Intervention conditions

#### Standard treatment

Participants randomized to ST are electronically connected with Tobacco Free Florida by the study team. Treatment consists of the standard treatment offered by Tobacco Free Florida, which is consistent with the Treating Tobacco Use and Dependence Clinical Practice Guideline [31, 32] in that treatment content is drawn from cognitive-behavioral and motivational interviewing techniques.

#### Motivation and problem solving+ (MAPS+)

MAPS + includes (1) 6 proactive, flexibly-offered telephone counseling sessions delivered over 12 months, and (2) proactive, text-based general and personally tailored treatment content delivered via SMS throughout the entire 24-month treatment period. The timing of the telephone counseling sessions during the first 12 months of the study period is determined jointly by the participant and their MAPS counselor. For example, participants struggling with maintaining abstinence may request several calls in a shorter period of time to get through the problematic period, whereas others prefer a less compressed counseling schedule and may need less frequent help. Each call lasts 30 min on average.

MAPS utilizes an innovative combination of motivational enhancement and social cognitive techniques, is designed for all individuals regardless of their readiness to quit, and specifically targets motivation, agency, and negative affect/stress. Counselors are trained to carefully assess and respond to changes in motivation so that treatment strategies are appropriately matched in the moment.

*General, non-tailored MAPS + text message content*. The general (i.e., non-tailored) text-based treatment content delivered via SMS is designed to provide information regarding general smoking cessation strategies and support as well as messages specifically related to participants’ diagnoses (i.e., CIN or cervical cancer). Treatment content delivery is less intensive in the first 12 months of the study period and increases slightly during months 13 through 24 to compensate for the end of human-delivered MAPS counseling support. Specifically, during the first 12 months, which runs concurrently with the human-delivered MAPS counseling delivery, participants receive 2 non-tailored text messages per week. In months 13 through 24, the frequency is increased to 3 non-tailored messages each week.

*Personally tailored MAPS + text message content*. In addition to the general treatment content delivered via SMS, MAPS + participants receive personalized text message-based treatment content which is delivered for the first week of every 30-day period throughout the entire 24-month treatment period. This personalized treatment content is tailored on participants’ self-reported smoking-status and their self-reported levels of motivation, agency, and negative affect/stress. Each construct is assessed using a single item. Specifically, every 30 days, participants receive smartphone-delivered prompts generated by REDCap to assess their need for support with both smoking-relevant issues and broader life issues including Wellness Program topics. In addition to asking about smoking status, motivation, agency and negative affect/stress, each monthly series of questions asks participants about key domains related to their Wellness Programs in which they may need support including physical activity, nutrition, hobbies, stress management, finances, sleep, and general wellness topics. As described above, the text-based treatment content is personalized on these 4 dimensions (i.e., smoking status, motivation, agency, and negative affect/stress. Participants can also choose to receive Wellness Program content in up to three topic areas. Participants who do not select specific Wellness Program topics receive text content related to general wellness topics. Throughout the entire 24-month study period, participants receive between 5 and 7 personally tailored text messages the first week of every 30-day period. For the remaining weeks, participants receive up to 3 personally tailored wellness program messages.

#### MAPS counselor qualifications and training

We have adopted the therapist selection criteria employed in major clinical trials of MI-based approaches: (1) master’s degree in counseling, psychology, social work, or a related field, and (2) 2 + years of clinical experience [33]. This, along with our training and ongoing monitoring, helps to ensure that the delivered treatment is of the highest quality. Counselors receive 20 h of MAPS training initially. Training continues until the counselor reaches performance criteria for competence and adherence to the protocol. Counselors participate in 1–2 h “booster” training sessions every 2 months. In addition, the counselors receive regular clinical supervision to discuss participants’ progress and to support adherence to the treatment manual.

#### MAPS counseling fidelity and monitoring

To monitor deviation or drift from the protocol, counseling calls are digitally recorded and encrypted. A random sample of 10% of calls is coded to ensure adequate adherence. A counselor who falls below performance criteria will receive additional training. The Motivational Interviewing Treatment Integrity Manual (MITI, 4th edition) [34] has empirically validated reliability and validity and is used to code sessions and ensure treatment fidelity. The MITI works well for ensuring that counselors are following the protocol and utilizing the general motivational interviewing spirit. In addition, the MITI is modified slightly to include coding of discussions around social cognitive/problem solving strategies and transitions between motivational enhancement and problem-solving. Weekly reports are reviewed to track call completion rates.

### Nicotine replacement therapy

All study participants receive 12 weeks of combination nicotine replacement therapy (patches + lozenges). Nicotine patches provide a low, constant level of nicotine, which attenuates nicotine withdrawal symptoms, and lozenges help with managing acute cravings to smoke. When combined with behavioral treatment, NRT doubles the odds of successfully quitting [26]. All participants receive educational materials describing potential side effects, proper use of the patch, and an illustration demonstrating the proper placement of the patch on the body. The nicotine patch and lozenge regimens are based on each participant’s self-reported smoking rate. Participants who smoke > 10 cigarettes/day receive 8 weeks of 21 mg patches, 2 weeks of 14 mg patches, 2 weeks of 7 mg patches, and 12 weeks of 2 mg lozenges. Those who smoke < = 10 cigarettes/day receive 8 weeks of 14 mg patches, 4 weeks of 7 mg patches, and 12 weeks of 2 mg lozenges.

### Measures

All study measures were selected based on established reliability and validity. If measures with established psychometric properties were not available, those chosen were required to have at least face validity. Assessments are given at baseline, 3, 6, 12, 18 and 24 months and require approximately 20 min to complete (see Table 1 for a list of all measures and assessment schedule).

**Table 1 Tab1:** Study measures and assessment schedule

Measure	Baseline Assessments	Smartphone Assessments (every 30 days)	Follow-Up Assessments (3, 6, 12, 18 and 24 months)
**DEMOGRAPHICS, SMOKING, SUBSTANCE USE, HEALTH HISTORY**			
Demographics and Smoking History	X		
History of CIN or Cervical Cancer	X		
Medical Comorbidities	X		
Cancer Patient – Tobacco Use Questionnaire (C-TUQ)	X		X
Heaviness of Smoking Index (HSI)	X		
Wisconsin Index of Smoking Dependence (WISDM-37)			X
Substance Use History	X		
Alcohol Use History (NIAAA)	X		X
Subjective Social Status	X		X
Health Literacy	X		
**MOTIVATION**			
Contemplation Ladder	X		X
Reasons for Quitting (Intrinsic and Extrinsic Motivation)	X		X
**AGENCY: SENSE OF CONTROL, SELF-EFFICACY, COPING BEHAVIOR**			
Sense of Control	X	X	X
Self-Efficacy Scale	X	X	X
Coping Inventory	X		X
**STRESS, NEGATIVE AFFECT, PSYCHOLOGICAL DISTRESS**			
Perceived Stress Scale (PSS-4)	X	X	X
Positive and Negative Affect Scale (PANAS)	X		X
Patient Health Questionnaire (PHQ-8)	X		X
**SMOKING ABSTINENCE**			
Smoking Status (SRNT)	X	X	X
**PATIENT REPORTED OUTCOMES**			
Functional Assessment of Cancer Therapy – Cervix Cancer (FACT-Cx)	X		X
Fear of Cancer Recurrence Inventory-Short Form*	X		X
**SATISFACTION WITH TREATMENT**			
Client Satisfaction Questionnaire (CSQ)			X**

*Modified for CIN participants as ‘Fear of Cancer’

**Only administered at 12- and 24-month follow-ups

Participants who report being abstinent from smoking at any follow-up assessment are mailed a prepaid envelope, instructions for providing a saliva sample, and a saliva collection kit. Research staff guide participants in providing the saliva samples and in returning the samples via mail.

#### Demographics, smoking history, alcohol and substance use, and health history

Demographic variables assessed include age, race, ethnicity, education, income, gender identity, sex assigned at birth, marital status, sexual orientation, occupational status and insurance status. Smoking history is assessed by asking about years smoking, preferred brand of cigarettes, quitting history, partner smoking, and the presence of other people who smoke in the household. The use of e-cigarettes (vaping) is also assessed. History of alcohol use is assessed using NIAAA core items [35, 36]. Substance use history is assessed with three items asking about illegal substance use in the past year.

History of CIN or cervical cancer is assessed by asking about diagnostic history, dysplasia grade or cervical cancer stage at the time of diagnosis, current CIN or cervical cancer stage, time since diagnosis, treatment status and time since completion of treatment.

The *Cancer Patient Tobacco Use Questionnaire (C-TUQ)* is a 22-item self-report survey designed to capture information about tobacco use by cancer patients and cancer survivors. The items are specifically tailored to the trajectory of cancer diagnosis, treatment, and survivorship. The C-TUQ survey tool is divided into five domains and includes a Core (short form of 4 items) and an Extension. The questionnaire is intended to be administered at key time points during periods of cancer treatment and recovery [37].

Nicotine dependence is assessed using the *Heaviness of Smoking Index (HSI)*. The HSI comprises two items from the Fagerstrom Test for Nicotine Dependence (FTND): self-reported average number of cigarettes smoked per day (CPD) and time to first cigarette upon waking (TTFC). The HSI is a good indicator of nicotine dependence, has fair internal consistency and is predictive of smoking relapse [38].

*The Wisconsin Index of Smoking Dependence Motives – Short Form (WISDM-37)* comprises 37 items designed to assess 11 different motivational domains: affective enhancement, affiliative attachment, automaticity, loss of control, cognitive enhancement, craving, cue exposure/associative processes, social/environmental goads, taste/sensory properties, tolerance, and weight control [39, 40].

The *Subjective Social Status* measure consists of a 10-rung ladder designed to represent different levels that a person may occupy within society. This scale has been shown to be a reliable measure of subjective social status among diverse populations and has shown a stronger relationship with health than many objective SES measures among those populations [41–43].

*Health literacy* is assessed using a single item, “How confident are you filling out medical forms by yourself?” [44] Responses are on a 5-point scale and include the following: 1 = “not at all,” 2 = “a little bit,” 3 = “somewhat,” 4 = “quite a bit,” and 5 = “extremely.” This single health literacy item has demonstrated adequate face, construct, content, and criterion validity for identifying individuals with limited health literacy in racially/ethnically diverse populations, [44–50] and is highly correlated with more comprehensive measures of health literacy including the REALM [51] and the STOFHLA [44, 45, 47–49, 52, 53]. Regarding scoring, the “somewhat” response has been identified as the optimal cut point to classify individuals as having limited health literacy [49]. Based on this recommendation and consistent with prior research, health literacy will be dichotomized as higher vs. lower (“not at all,” “a little bit,” or “somewhat” = low; “quite a bit” or “extremely” = high) [45, 49].

#### Motivation for smoking cessation

The *Contemplation Ladder* assesses readiness to quit smoking on an 11-point “ladder” scale with steps ranging from 0, “no thought of quitting,“ to 10, “taking action to quit” (e.g., cutting down, enrolling in a program) [54].

The *Reasons for Quitting (Intrinsic and Extrinsic Motivation)* measure is a 20-item scale that assesses intrinsic (health concerns, self-control) and extrinsic (immediate reinforcement, social influence) motives for quitting smoking. Both intrinsic motives and the ratio of intrinsic to extrinsic motives have been demonstrated to predict successful smoking cessation [55].

